### Data sources

The study will use routinely collected data from various population health registries with national comprehensive scope. Each database contains a unique identifier for each individual to allow data linkage between databases. We have not yet received any access to the data at the time of submission of this study protocol but have previous experience in studies using this approach [1–6]. The National Health Service User (NHSU) dataset is the reference population database and includes individual records of the target study population. For this study, we will only consider individuals who had contact with the NHSU healthcare system three years before the start of the study period to account for health seeking behaviour and likelihood to have a vaccine recommended. Vaccination registry or vaccination record databases with individual data, including influenza and vaccine brand dates, will be provided by the National Vaccination Registry – VACINAS. VACINAS is the national vaccination registry, that is accessible to all health professionals who administer the vaccine (in both the public and private sectors) and vaccine registration is mandatory. Primary healthcare data on diagnoses, chronic conditions, and eligibility for the influenza vaccine - SIM@SNS, which is the data platform for patient management at PC. Regarding the outcome, the National Hospital Discharges Registry will be used to assess hospitalisation information (BDMH and BIMH), which is used for public hospital management and centralizes data from mainland Portugal. Hospital discharge codification is conducted by trained medical doctors using ICD-10 codes.

### Construction of the cohort

#### Identification of individuals and characteristics at baseline.

The reference population database will be linked with the electronic databases on vaccination, comorbidities and/or health-seeking behaviour, hospitalisations and other vital registries, using the unique identifiers through a deterministic data linkage procedure (no random component in the linkage procedure). Individuals will enter the study in their corresponding vaccination status group based on the data available in the vaccination registry.

Variables to be measured at baseline include age, sex, health administrative region, comorbidities, and other socioeconomic or health-seeking behaviour variables that will be used to adjust IVE estimates to stratify or account for confounding.

#### Time-changing characteristics (to estimate absolute IVE).

Vaccination status and time since vaccination will be assessed, and individuals will be classified into the same or updated vaccination status daily, generating a new record in the dataset for each new assessment. Person-time exposure between 0 and 13 days after vaccination will be excluded from the analysis.

#### Identification of outcomes during follow-up.

Information for identifying outcomes and the dates when they occurred will be obtained by data linkage between the cohort built previously and the databases containing information on the respective outcomes. Outcome classification for each individual will be assessed from the start of the vaccination campaign.

#### Censoring events.

All individuals will be followed from the start of the vaccination campaign until:

◦ Hospitalisation date (corresponding to the event date);◦ At the end of the study (nine months after the start of the vaccination campaign);◦ On the date of death (any cause)

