## Methods

### Study design and population

A retrospective cohort study using data collected routinely in EHR databases will be implemented. For the estimation of rIVE, only vaccinated individuals will be included, either with the high-dose or the standard influenza vaccine. For the estimation of absolute IVE, individuals eligible for the high-dose influenza vaccine during the study period will be included. For both cohorts, we will consider two subgroups: community-dwelling individuals aged ≥85 years and individuals living in LTCF. The cohorts are represented in Fig 1, with panel A representing rIVE and panel B absolute IVE.

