### Inclusion and exclusion criteria

The study population includes all registered individuals without contraindications for influenza vaccination residents in mainland Portugal. Only vaccinated individuals with the high-dose quadrivalent or standard influenza vaccine living in LTCF or community-dwelling individuals aged 85 or older will be included to estimate rIVE. Whereas, to estimate absolute IVE, only eligible individuals for the high-dose influenza vaccine living in LTCF or community-dwelling individuals aged 85 or older will be included.

We will exclude individuals with inconsistent or missing data on vaccination (e.g., any vaccination date unknown and any vaccine brand unknown), individuals who received any vaccine brand not approved by the European Medicines Agency (EMA), and individuals vaccinated before the study started.

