### Vaccination status

To estimate rIVE, the vaccination status will be assessed retrospectively, and the time since vaccination will be estimated. The exposure of interest will be to receive the high-dose quadrivalent influenza vaccine, and the comparison group will be composed of those who received the standard-dose influenza vaccine.

To estimate absolute IVE, the vaccination status will be assessed as a time-changing variable according to the following classification:

◦ Unvaccinated: person-time of individuals without any quadrivalent influenza vaccine in the season.◦ Vaccinated: person-time of individuals who received a high-dose quadrivalent influenza vaccine dose during the study period. The completion status is achieved 14 days after administration of the dose.

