### Estimation of the vaccine effectiveness

A complete case analysis will be performed considering all variables in the final model to estimate adjusted-confounding IVE and stratified for each subgroup, individuals linving in LTCF and individuals living in the community (≥85 years)

We will use Cox proportional hazards regression models to estimate the hazard ratio (HR), considering the event the first hospitalisation due to influenza-like-illness and as exposure the vaccination status. The crude HR of vaccinated with the high-dose influenza vaccine vs vaccinated with the standard dose (rIVE) or unvaccinated (absolute IVE) will be estimated for each outcome of interest during the study period, without adjusting for other factors or covariates.

We will consider two sets of confounding factors. First, we will estimate partially adjusted HR, adjusting by age, sex and country region. Age will be modelled using a restricted cubic spline, with knots specified according to Harrell [12]. Second, a fully adjusted HR estimate will be produced by adjusting variables related to socioeconomic condition, comorbidities and health-seeking behaviour. IVE will be estimated as one minus the confounder-adjusted HR of vaccinated vs vaccinated with the standard dose (rIVE) or unvaccinated (absolute IVE) for each outcome of interest.

IVE = (1 - aHR) * 100

To estimate relative IVE, the time since vaccination will be modelled using a restricted cubic spline, with knots specified at zero and 15 days and then at the 40^th^ and 90^th^ percentile. To estimate absolute IVE for the time since vaccination (secondary objective), IVE will be estimated by comparing the hazard rate of the outcome in individuals vaccinated with the high-dose influenza vaccine for each class of the time since vaccination - 14–89 days, 90–179 days and 180–272 days (exposed group), in comparison with the outcome hazard rate in unvaccinated individuals (reference group).

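### Relative-IVE follow-up starts at the campaign start, before the dose that defines the cohort and its groups, so pre-dose time and events are credited to the vaccine received later

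*Protocol article*

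**What the plan says.** **Time origin.** The protocol article, under Censoring events, states: "All individuals will be followed from the start of the vaccination campaign until" hospitalisation, death or the end of the nine-month study. Under Identification of outcomes during follow-up it adds: "Outcome classification for each individual will be assessed from the start of the vaccination campaign". Neither sentence separates the two cohorts.

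**Membership and grouping for rIVE.** Study design and population: "For the estimation of rIVE, only vaccinated individuals will be included, either with the high-dose or the standard influenza vaccine". Inclusion and exclusion criteria removes "individuals vaccinated before the study started", so every qualifying dose falls on or after study start. Vaccination status: "To estimate rIVE, the vaccination status will be assessed retrospectively, and the time since vaccination will be estimated". Identification of individuals and characteristics at baseline: "Individuals will enter the study in their corresponding vaccination status group based on the data available in the vaccination registry".

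**Where time is handled differently.** Vaccination status makes exposure time-changing for absolute IVE only. The rule "Person-time exposure between 0 and 13 days after vaccination will be excluded from the analysis" stands under a heading restricted to absolute IVE. For rIVE the only time element is a model term: "the time since vaccination will be modelled using a restricted cubic spline, with knots specified at zero and 15 days", with further knots at the 40th and 90th percentiles (Estimation of the vaccine effectiveness).

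**The concern.** In the rIVE cohort the clock starts before the event that decides both who is in the cohort and which group they are in. Three kinds of time then sit under one high-dose or standard-dose label.

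- **Before the dose.** Nobody in the cohort can die here, because a dead person is never vaccinated. Hospitalisation is less clear-cut. Someone admitted and later vaccinated counts as an event for that vaccine, while someone admitted and never vaccinated is absent from the cohort. The article does not say how such people are handled.
- **Days 0–13 after the dose.** This time is removed for absolute IVE but kept for rIVE.
- **From day 14.** This is the only time in which the two vaccines can be expected to differ.

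Mixing them dilutes a true difference even when both groups are vaccinated on the same dates. If dose dates differ between groups, the pre-dose contribution does not cancel and the estimate can move either way. rIVE is a stated objective meant to inform national vaccine policy. The only rIVE figure cited in the Background is 11.2% (7.4%–14.8%), so a shift of a few points matters.

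**Working it through.** The article gives no sample size, event count or dose dates, so there is no planned figure to reproduce. The numbers below are illustrations.

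**Inputs**
- From the article: rIVE 11.2% (Background); IVE = (1 − HR) × 100; nine months of follow-up.
- Assumed: unvaccinated hazard = standard-dose hazard / 0.7, i.e. a relative hazard u = 1/0.7 = 1.43 that also applies on days 0–13; an epidemic wave with SD 20 days and a stated peak day; doses spread evenly over a stated window from campaign start.
- Unknown, so taken at both extremes: q, the share of people hospitalised before the dose who are later vaccinated and so stay in the cohort (0 or 1).

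**Equal dose timing, by hand.** Let A, B and P be the shares of the epidemic falling before the dose, on days 0–13, and from day 14 (A + B + P = 1). For rare events:

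HR ≈ [u(qA + B) + 0.888P] / [u(qA + B) + P]

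so observed rIVE ≈ 11.2% × P / [u(qA + B) + P].

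- Peak day 60, both windows days 0–60: A = 0.133, B = 0.147, P = 0.720.
  - q = 0: 11.2 × 0.720 / (0.210 + 0.720) = 8.7%.
  - q = 1: 11.2 × 0.720 / (0.400 + 0.720) = 7.2%.
  - A day-by-day Cox calculation gives 8.7% and 7.3%.
- Peak day 105, same windows: A = 0.001, B = 0.007, P = 0.991. With q = 0: 11.2 × 0.991 / (0.010 + 0.991) = 11.1%.

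**Unequal timing, day-by-day Cox model, no spline** (HD = high dose, SD = standard dose)

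| Peak day | Dose windows (days) | rIVE, q = 0 | rIVE, q = 1 |
|---|---|---|---|
| 105 | HD 0–30, SD 0–120 | 1.4% | 19.5% |
| 105 | HD 0–120, SD 0–30 | 18.4% | −1.8% |

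With one window days 0–30 and the other days 0–90, taking both orders and both values of q, the range is 1.6–17.4% at peak day 90, 7.0–14.1% at day 105 and 9.9–12.1% at day 120. In a separate set with standard-dose effectiveness of 40%, peak day 60 and typical dose days 30 days apart, the range is −17.6% to 25.3%.

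**The planned spline.** Entered as a time-updated covariate (days since dose, negative before it):
- HD 0–30 and SD 0–120 at peak day 105 gives 8.4% (q = 0) and 10.5% (q = 1), against 1.4% and 19.5% without it.
- Equal 0–60 windows at peak day 60 still give 7.3–8.7%. The term has the same distribution in both groups, while the model still applies one hazard ratio to time in which the vaccines cannot differ.
- Very unequal windows with an early peak give 5.6–13.7%.
- The widest windows are sensitive to coding: 12.7% was also obtained where 8.4% is shown.

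If the covariate is instead taken once, at exit, it is a function of the event time. The article does not say which is meant.

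**Entry 14 days after each person's own dose** returns 11.2% in every scenario, by construction: all remaining time has the assumed hazard ratio, and both groups share the calendar hazard.

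**The case against.** The strongest reply has four parts.

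1. **The spline is part of the planned model**, and figures computed without it are not what the plan would return. This largely stands. A restricted cubic spline is defined, and linear, below its first knot, and knots at 0 and 15 days can model the early post-dose period. As a time-updated covariate it removes much of the bias from unequal timing. It does not remove the dilution, and nothing in the article says it is time-updated.
2. **Nothing shows that dose dates differ between groups.** A reader might infer this from the different access routes for high dose in the Background. That passage describes access and co-payment and gives no dates. Estimates are stratified by setting and, when applicable, by season, so the inference is unsupported. Equal timing cannot be presumed either.
3. **Study setting and period starts the rIVE period after implementation of each campaign**, which is looser wording than Censoring events. It is still a common calendar start, not a personal dose date, and the two sections need reconciling.
4. **Pre-dose time is not immortal for hospitalisation.** Correct: it is strictly so only for death. The handling of people hospitalised before their dose remains unstated, and that alone spans 1.4% to 19.5% in the widest no-spline case.

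Propensity score matching on baseline characteristics does not move the time origin, and vaccination date is not among the listed confounders.

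**Conclusion.** The time-origin rule is wrong as written for rIVE. No section gives that cohort a dose-based entry, and the safeguards against misplaced person-time are confined to absolute IVE.

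The size is uncertain. Under the stated assumptions the bias is negligible with equal dose timing and a late epidemic (about 11.1% against 11.2%). With equal timing and an early epidemic it is a dilution to about 7–9%. With unequal timing it can reach 10 points or more either way if the spline is ignored. With a time-updated spline it mostly stays within about 3 points for peaks at day 90 or later, and within about 6 points for an early peak.

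A reader might go further and conclude that rIVE will be off by the full no-spline amounts, or in a known direction. The documents do not support that: they give no dose dates or epidemic timing, and they do include the spline.

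**What to change.** For the rIVE cohort only, amend Study setting and period, Identification of outcomes during follow-up, Censoring events, and Estimation of the vaccine effectiveness so that:

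- each person's follow-up starts 14 days after their own dose (delayed entry), provided they are alive and have had no outcome event by that date;
- calendar time is accounted for, by using it as the Cox time scale or by adjusting for or matching on vaccination date;
- the time-since-vaccination term is defined to agree with the new origin, stating whether it is time-updated. Replacing it with calendar week of vaccination is one reasonable option, not a requirement.

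Keep campaign start as time zero for absolute IVE, where exposure is already time-changing.

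The cost is rewording, a delayed-entry term and the loss of events before day 14, which are few if most doses precede the epidemic. No new data are needed, and the article states that data had not been accessed at submission.

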### Analysis plan

#### Description of the sample selection.

The total number of individuals fulfilling the inclusion criteria at the study baseline will be calculated for each cohort. The number and proportion of individuals excluded after applying each selection criteria will be recorded.

#### Description of the study population.

The number of persons, total person-time of follow-up, and the number of events by vaccination status will be calculated. Distribution of the number of persons and total person-time of follow-up will be described by baseline variables in each vaccination status group considered in the study. To estimate the total number of persons, we will consider the vaccination status group at the end of each person-time follow-up (to estimate absolute IVE).

The proportion of the missing data will be used to determine if each specific variable can be included in the model and how (e.g., missing could eventually be included in the model as a category). Imputation to address missingness is not planned as a means for increasing data quality.

### Estimation of the vaccine effectiveness

A complete case analysis will be performed considering all variables in the final model to estimate adjusted-confounding IVE and stratified for each subgroup, individuals linving in LTCF and individuals living in the community (≥85 years)

We will use Cox proportional hazards regression models to estimate the hazard ratio (HR), considering the event the first hospitalisation due to influenza-like-illness and as exposure the vaccination status. The crude HR of vaccinated with the high-dose influenza vaccine vs vaccinated with the standard dose (rIVE) or unvaccinated (absolute IVE) will be estimated for each outcome of interest during the study period, without adjusting for other factors or covariates.

We will consider two sets of confounding factors. First, we will estimate partially adjusted HR, adjusting by age, sex and country region. Age will be modelled using a restricted cubic spline, with knots specified according to Harrell [12]. Second, a fully adjusted HR estimate will be produced by adjusting variables related to socioeconomic condition, comorbidities and health-seeking behaviour. IVE will be estimated as one minus the confounder-adjusted HR of vaccinated vs vaccinated with the standard dose (rIVE) or unvaccinated (absolute IVE) for each outcome of interest.

IVE = (1 - aHR) * 100

To estimate relative IVE, the time since vaccination will be modelled using a restricted cubic spline, with knots specified at zero and 15 days and then at the 40^th^ and 90^th^ percentile. To estimate absolute IVE for the time since vaccination (secondary objective), IVE will be estimated by comparing the hazard rate of the outcome in individuals vaccinated with the high-dose influenza vaccine for each class of the time since vaccination - 14–89 days, 90–179 days and 180–272 days (exposed group), in comparison with the outcome hazard rate in unvaccinated individuals (reference group).

#### Propensity score matching.

Individual characteristics might influence vaccination status, leading to systematic differences between those vaccinated with different vaccines and those vaccinated (rIVE) and unvaccinated (absolute IVE). Propensity score matching is a statistical technique used to reduce selection bias in observational studies by creating a matched set of treated (vaccinated with high-dose influenza vaccine) and untreated (vaccinated – rIVE and unvaccinated – absolute IVE) individuals with similar propensity scores. The first option will be matching without replacement, 1-to-1. However, considering the vaccination coverage, this ratio might need to be reviewed.

Several assumptions should be met to ensure that conditioning on the propensity score will lead to unbiased estimates of average treatment effects. The first one is that there should not be unmeasured confounders, i.e., the variables affecting vaccination status and hospitalisation due to influenza-like-illness should have been measured. The second relates to positivity, each individual should have a non-zero probability of getting the high-dose influenza vaccine. Additionally, the propensity score model should be correctly defined, and there should not be any interference between individuals, i.e., an individual vaccinated with the high-dose influenza vaccine will not affect the hospitalisation of another individual. This final assumption has implications in estimating absolute IVE studies due to herd immunity since vaccinated individuals could indirectly protect unvaccinated individuals, leading to IVE underestimation. To account for potential violations of this assumption, we will consider statistical methods that account for clustering, which could be the geographical region of residence.

The propensity score will be estimated using logistic regression, where the vaccination status will be the outcome, and the baseline individual characteristics will be used to adjust. Then, the vaccinated with high-dose influenza vaccine and vaccinated (rIVE) or unvaccinated (absolute IVE) individuals with similar propensity scores will be matched, using nearest neighbour matching, and compared to ensure the balance of covariates. Once the balanced dataset is obtained, the Cox proportional hazards regression model will be used, with the adjustments mentioned in the section above to adjust for residual confounding [13].

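### Absolute IVE: person-level propensity matching uses a vaccination status reached only during follow-up, which can bias the time-varying Cox estimate by an amount and in a direction the protocol does not settle

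*Protocol article*

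**What the plan says.** Four parts of the Protocol article bear on absolute IVE.

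- **Time zero.** Under Censoring events: "All individuals will be followed from the start of the vaccination campaign until" admission, death or nine months. Inclusion and exclusion criteria removes "individuals vaccinated before the study started". So nobody is vaccinated when follow-up begins.
- **Exposure.** Under Vaccination status: "To estimate absolute IVE, the vaccination status will be assessed as a time-changing variable". Under Time-changing characteristics: "individuals will be classified into the same or updated vaccination status daily, generating a new record in the dataset for each new assessment". Person-time on days 0 to 13 after a dose is dropped.
- **Matching.** Under Propensity score matching, the score is "estimated using logistic regression, where the vaccination status will be the outcome, and the baseline individual characteristics will be used to adjust". Vaccinated and unvaccinated individuals are paired by nearest neighbour: "The first option will be matching without replacement, 1-to-1". The ratio may be reconsidered in view of coverage.
- **Order.** "Once the balanced dataset is obtained, the Cox proportional hazards regression model will be used".

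No matching date, risk set or rule for controls vaccinated later is given. The only rule that gives each person a single status is in Description of the study population. It takes the status at the end of follow-up, and it serves descriptive counts.

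**The concern.** A logistic model with one row per person needs one vaccination status per person. At time zero that status is the same for everyone, so the model can only use one acquired later. Grouping people by it conditions on the future. Anyone admitted or dying before a planned dose counts as unvaccinated, while everyone in the vaccinated pool is known to have stayed event-free up to the dose.

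A time-dependent Cox model on the full cohort copes with this, because both kinds of unvaccinated person-time stay in each risk set in their true proportions. Matching after the split keeps different fractions of the two pools and changes those proportions. The Discussion relies on this matching to deal with differences between vaccinated and unvaccinated people. A step meant to reduce selection bias could add some, and a table of balanced baseline covariates would not reveal it.

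**Working it through.** The protocol states no coverage, event count or target precision, so there is no figure of its own to reproduce.

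**Why the hazard shifts.** On day t, split the unvaccinated people at risk into L (vaccinated later in their follow-up) and N (never vaccinated in their follow-up). All unvaccinated events that day come from N, since an event ends follow-up. Let s1 and s0 be the fractions of the ever-vaccinated and never-vaccinated pools that matching keeps. Then

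matched unvaccinated hazard ÷ true unvaccinated hazard = s0(N + L) / (s0·N + s1·L).

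The vaccinated hazard is unchanged, because s1 cancels. The ratio is 1 if s0 = s1, or once roll-out is over (L = 0).

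**One day by hand.** Assume even uptake, halfway through roll-out, 1:1 matching, true HR 0.60, and ignore losses.

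- 80% coverage: L = 0.40, N = 0.20, s0 = 1, s1 = 0.20/0.80 = 0.25. Ratio = 0.60/(0.20 + 0.10) = 2. That day's HR is 0.60/2 = 0.30, an IVE of 70%.
- 50% coverage: s0 = s1, ratio 1, IVE 40%.
- 20% coverage: L = 0.10, N = 0.80, s1 = 1, s0 = 0.25. Ratio = (0.25 × 0.90)/(0.20 + 0.10) = 0.75. That day's HR is 0.60/0.75 = 0.80, an IVE of 20%.

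The season estimate averages such days with the unbiased days after roll-out.

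**Whole season.** This is an expected-value Cox calculation on 272 daily steps. Assumed inputs, none from the protocol: no confounding (so random selection within pools stands for perfect balance), 3% cumulative event risk, 10% deaths, even uptake over 90 days, true IVE 40%, and nobody vaccinated after an admission. Hazards are flat or peaked with SD 25 days. The full-cohort time-varying Cox model returns 40.0%. After 1:1 matching:

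| Coverage | Flat hazard | Peak day 60 | Peak day 100 |
|---|---|---|---|
| 20% | 38.0% | 30.5% | 38.3% |
| 50% | 39.9% | 39.5% | 39.9% |
| 65% | 41.9% | 47.0% | 41.7% |
| 80% | 46.1% | 59.1% | 45.6% |

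For a vaccine with no effect, the day-60 peak gives about -17% at 20% coverage and about 33% at 80%.

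**Independent simulation** (1.5 million persons per run, Monte Carlo error about 1 to 2.5 points, true IVE 40%). The full cohort gave 38.5% to 40.9%. In the order flat, day-60, day-100, matching gave 37.9%, 32.9% and 39.3% at 30% coverage, and 44.5%, 53.5% and 44.7% at 75%.

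**Where the effect shrinks** (true IVE 40%):

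- Even 60-day uptake: 37.1% to 40.0% at 20% coverage, 40.0% to 42.7% at 65%, 40.1% to 48.6% at 80%.
- Front-loaded 90-day uptake (20-day decay): 37.7% to 39.9% at 20%, 40.2% to 47.4% at 80%.
- More controls per case at 20% coverage, day-60 peak, even 90-day uptake: 30.5% at 1:1, 36.8% at 1:2, 39.9% at 1:4.
- Status read from the registry at season end, with vaccination unrelated to the admission: 39.0% to 41.6% in the simulation.

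**The case against.** The strongest reply is that the faulty step is inferred. The protocol does not say when the status is taken, the article is a condensed document, and a score fitted to the daily records is not excluded word for word. It is true that the date is not stated. But the text describes baseline characteristics, matching of individuals and a Cox model fitted afterwards, and no reading of that sequence puts the status at time zero. This is a described procedure that goes wrong if followed, so it is more than a missing detail.

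The reply on size largely stands. The Discussion suggests only that coverage may be low, which makes the high-coverage figures a poor headline. The bias vanishes near 50% coverage and reverses below it. It is small when events follow roll-out, and it depends on a ratio that the protocol leaves open. If people admitted early are still vaccinated and counted, it nearly disappears, but that requires an admission not to affect later vaccination, which nothing in the protocol establishes.

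It is also fair that Estimation of the vaccine effectiveness describes unmatched Cox models that do not have this fault, and that the matched result is not labelled primary.

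Two stronger readings are tempting. One is that the plan will inflate absolute IVE; without coverage and timing, the sign is unknown. The other is that the matched groups would be analysed as fixed from campaign start, with a large immortal-time bias; the daily-updated exposure rules that out.

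**Conclusion.** The concern holds in limited form. For absolute IVE, matching as described selects people on a status acquired after time zero and can bias an otherwise sound time-varying Cox estimate, unseen by baseline balance checks. With a true IVE of 40%, the assumed scenarios give about 31% to 59%. Both extremes need even 90-day uptake, an event peak during roll-out, 1:1 matching and no vaccination after early admission. With faster uptake most scenarios lie within a few points of 40%, although 80% coverage with a day-60 peak still reaches 47% to 49%. Coverage, uptake, event timing and mortality are all assumptions. This should be fixed, but it does not invalidate the full-cohort analysis, and it does not extend to relative IVE.

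**What to change.** For absolute IVE, adopt one of two designs and state it in the protocol.

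1. Drop person-level matching, and enter the baseline propensity score, or its covariates, in the full-cohort time-dependent Cox model already described under Estimation of the vaccine effectiveness.
2. Match on calendar date: pair each new high-dose recipient with someone alive, event-free and still unvaccinated on that date. Start both 14 days later, and censor the pair when the control is vaccinated.

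The full-cohort model on which the first option builds recovered the true value in the calculations above. The second avoids future status by construction but was not simulated. Relaxing the matching ratio alone is not a remedy, since it only changes the sampling fractions and therefore the bias.

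The first option costs programming only. The second also loses late control person-days through censoring, which lowers precision, notably in the 180 to 272 day class of time since vaccination.
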